## Abstract

**Background:**

Aortic valve replacement is one of the most common cardiac surgical procedures performed worldwide. Conventional aortic valve replacement surgery is performed via a median sternotomy; the sternum is divided completely from the sternal notch to the xiphisternum. Minimally invasive aortic valve replacement, using a new technique called manubrium-limited ministernotomy, divides only the manubrium from the sternal notch to 1 cm below the manubrio-sternal junction.

More than one third of patients undergoing conventional sternotomy develop clinically significant bleeding requiring post-operative red blood cell transfusion. Case series data suggest a potentially clinically significant difference in red blood cell transfusion requirements between the two techniques. Given the implications for National Health Service resources and patient outcomes, a definitive trial is needed.

**Methods/design:**

This is a single-centre, single-blind, randomised controlled trial comparing aortic valve replacement surgery using manubrium-limited ministernotomy (intervention) and conventional median sternotomy (usual care). Two hundred and seventy patients will be randomised in a 1:1 ratio between the intervention and control arms, stratified by baseline logistic EuroSCORE and haemoglobin value. Patients will be followed for 12 weeks from discharge following their index operation. The primary outcome is the proportion of patients who receive a red blood cell transfusion post-operatively within 7 days of surgery. Secondary outcomes include red blood cell and blood product transfusions, blood loss, re-operation rates, sternal wound pain, quality of life, markers of inflammatory response, hospital discharge, health care utilisation, cost and cost effectiveness and adverse events.

**Discussion:**

This is the first trial to examine aortic valve replacement via manubrium-limited ministernotomy versus conventional sternotomy when comparing red blood cell transfusion rates following surgery. Surgical trials present significant challenges; strengths of this trial include a rigorous research design, standardised surgery performed by experienced consultant cardiothoracic surgeons, an agreed anaesthetic regimen, patient blinding and consultant-led patient recruitment. The MAVRIC trial will demonstrate that complex surgical trials can be delivered to exemplary standards and provide the community with the knowledge required to inform future care for patients requiring aortic valve replacement surgery.

**Trial registration:**

International Standard Randomised Controlled Trial Number (ISRCTN) ISRCTN29567910. Registered on 3 February 2014.

**Electronic supplementary material:**

The online version of this article (doi:10.1186/s13063-016-1768-4) contains supplementary material, which is available to authorized users.

## Background

### Aortic valve replacement (AVR)

AVR is one of the most common cardiac surgical procedures performed worldwide [1, 2]. Patients suffer symptoms of chest pain, shortness of breath and dizziness as a result of aortic stenosis or regurgitation. Nearly 10,000 patients undergo AVR surgery in the UK every year [2]. Patient outcomes of AVR performed in the UK from 2004 to 2009 [3] showed a 26% increase in the number of patients undergoing surgery during this period. At The James Cook University Hospital (JCUH) in the North of England, an audit over the same time period confirmed a 24% increase in the number of AVR operations. It is anticipated that the number of AVR operations will continue to increase.

### Blood transfusion following AVR

There is significant morbidity associated with AVR surgery. Consequently, blood loss and the subsequent requirement for transfusion of red blood cells (RBCs) and blood products are key indicators of quality. More than one-third of patients undergoing conventional sternotomy develop clinically significant bleeding and require a post-operative RBC transfusion [4, 5]. Blood transfusion can have adverse clinical effects including post-operative lung injury, organ dysfunction, confusion, and immunosuppression [6]; complications of transfusion have been directly linked to prolonged hospital stay and increased mortality after cardiac surgery [5, 7–12]. Additionally, there is a small risk of transmitting viral infection from blood donor to recipient [13]. Currently, cardiac surgical procedures use 6% of all donor blood available in the UK [14]. An analysis of patients over 5 years from the Society for Cardiothoracic Surgery in Great Britain and Ireland National Database indicated that of 41,227 patients who underwent AVR surgery, 2342 (6%) required a second operation due to excessive bleeding [3].

Retrospective studies have shown that blood loss and transfusion requirements are significantly less with minimally invasive AVR [15–17]; however, most reported using a fourth space ministernotomy incision rather than a manubrium-limited approach. No study thus far has tested RBC transfusion requirements in a randomised controlled trial using manubrium-limited ministernotomy.

## Rationale for choice of comparators'

### Surgical techniques in AVR

#### Usual care: conventional sternotomy

Conventional surgery for AVR is performed via a median sternotomy, in which the sternum is divided completely from the sternal notch to the xiphisternum. The operation includes cardiopulmonary bypass established by siting cannulas in the right atrium and ascending aorta. The heart is stopped and the valve is replaced.

#### Intervention under study: minimally invasive ministernotomy

The new technique of manubrium-limited ministernotomy divides only the top quarter of the sternum from the sternal notch to 1 cm below the manubrio-sternal junction; this enables access to perform the AVR. Potential benefits may include reductions in bleeding, post-operative pain, inflammatory response, hospital stay and time away from work. The cardiothoracic surgical community are enthusiastic about the procedure; however, they are clear that definitive benefit needs to be demonstrated in a randomised controlled trial before widespread adoption of the technique.

### Inflammatory markers

In minimally invasive cardiac surgical procedures, there is less tissue trauma and the right atrium is not directly cannulated; conversely, cardiopulmonary bypass and aortic cross-clamp times are longer. The mechanism for any observed benefits of the minimally invasive approach is unconfirmed, but may be due to a difference in systemic inflammatory response (SIR). SIR can be measured by monitoring the profile of cytokines in plasma.

This trial will determine if there is a difference in SIR to AVR via manubrium-limited ministernotomy when compared to conventional sternotomy by measuring inflammatory markers at pre- and post-surgical time points. We will seek to understand the mechanism underlying the observations we make. Our hypothesis is that patients who receive a sternotomy will bleed more and require more blood transfusions. The excess bleeding might be a direct result of the increased surgical trauma or as a result of an increased SIR to sternotomy. A SIR may have wide-ranging post-operative effects and has previously been shown to increase atrial fibrillation and acute kidney injury, impair wound healing and reduce post-operative haemostasis [18].

### Trial rationale

Case series data at The JCUH suggest a potentially significant and clinically important difference in the need for RBC transfusion when comparing patients undergoing conventional and manubrium-limited surgery. Given the implications of transfusion for National Health Service (NHS) resources and patient outcomes, and the potential benefits from this new technique, there is a need for a definitive trial. There has been one trial in the UK evaluating the fourth space median (minimally invasive) sternotomy (PB-PG-0408-16296; ISRCTN 58128724); this trial is now closed to recruitment and is in follow-up. Thus far, no randomised trial has compared manubrium-limited ministernotomy to conventional sternotomy for AVR.

The need for AVR is increasing and, with an ageing population, the balance of surgical risk will become less favourable given the greater level of co-morbidity in older populations. Importantly, this new approach also has the potential to reduce the risk of post-operative lung injury, organ dysfunction and immunosuppression, as well as reduce the burden on already overstretched blood transfusion services. A robust trial of the manubrium-limited technique compared with conventional surgery is imperative and timely to ensure that appropriate surgical strategies deliver improved patient outcomes and efficient use of scarce NHS resources.

The trial will run according to the principles of International Conference on Harmonisation (ICH)-Good Clinical Practice (GCP) and in accordance with relevant UK legislation and the trial protocol.

## Methods/design

### Objectives

This trial will investigate whether new manubrium-limited surgery (intervention) reduces RBC transfusion rates compared to conventional cardiac surgery (control) for patients undergoing aortic valve replacement. The null hypothesis is that there will be no difference in the proportion of patients receiving RBC transfusion after manubrium-limited ministernotomy when compared to conventional sternotomy for AVR.

### Trial design

This is a single-centre, single-blind, randomised controlled superiority trial comparing patients undergoing AVR via manubrium-limited ministernotomy (intervention under study) or conventional median sternotomy (control arm/usual care); randomisation will be performed using random permuted blocks with a 1:1 allocation.

The manubrium-limited ministernotomy versus conventional sternotomy for aortic valve replacement (MAVRIC) trial protocol was written in accordance with the Standard Protocol Items: Recommendations for Interventional Trials (SPIRIT) checklist (see Additional file 1) [19, 20]. The schedule of this trial is shown in Fig. 1.

**Fig. 1 Fig1:**
[figure not shown]
Schedule of enrolment, intervention and assessments for the MAVRIC trial

### Trial setting

The study aims to recruit 270 patients in a single NHS Trust in the North of England.

### Eligibility criteria

#### Inclusion criteria

Patients are eligible for the study if they:Are aged 18 years or older at the time of consentRequire first-time, non-emergency, isolated AVR; surgeryAre able; and willing to provide written informed consent.

#### Exclusion criteria

Patients are excluded from entering the study if they:Require concomitant cardiac procedure(s)Have a haemoglobin level <90 g/LAre pregnant; Are unable to stop currently prescribed treatment affecting clottingHave a haematological condition that would affect participation in the trialHave infective endocarditisAre prevented from having RBCs and blood products according to a system of beliefsHave any other medical, psychiatric and or social reason that precludes participation.

#### Eligibility check

Participants have their eligibility checked and confirmed within the 14 days prior to surgery. Eligibility is confirmed by one of the three operating cardiac surgeons who are clinical investigators for this trial.

### Interventions

#### Manubrium-limited ministernotomy (intervention)

Manubrium-limited ministernotomy (intervention arm) is performed using systemic normothermia. An incision is made from the sternal notch to the second intercostal space. The manubrium is divided longitudinally in the midline. The sternum is then transected in both directions from the second intercostal spaces until the midline incision is reached, creating a V shape. This procedure is depicted in Fig. 2. Aortic cannulation is through the ascending aorta. As the right atrium is poorly visualised with this technique, venous cannulation is percutaneous through the femoral vein (using a Seldinger technique guided by transoesophageal echocardiography). Vacuum assist is used as necessary to aid venous drainage. Antegrade cardioplegia is used for myocardial protection, and venting is via the pulmonary artery. A transverse aortotomy is performed, followed by standard aortic valve insertion using interrupted nonpledgeted braided sutures. The aortotomy is closed in a single or double layer. One pericardial drain and ventricular pacing wires are placed in all patients. Atrial wires are placed if needed. These steps are performed prior to removing the cross-clamp to facilitate the view of the right atrium and ventricle. The sternum is closed with two wires in the manubrium and two wires from the body of the sternum up to the manubrium.

**Fig. 2 Fig2:**
[figure not shown]
Division and transection of the sternum in a manubrium-limited ministernotomy

#### Conventional median sternotomy (control)

For the conventional technique, a standard median sternotomy is performed using systemic normothermia. Cannulation is via the ascending aorta with two-stage right atrial cannulation for venous drainage. Venting of the left ventricle is achieved via the pulmonary artery, and myocardial protection is with cold blood antegrade cardioplegia. All valves are inserted using interrupted sutures.

During the trial, both operations are performed in accordance with an agreed and standardised anaesthetic protocol. Patients are given lorazepam as a pre-medication, followed by anaesthesia with propofol, fentanyl, rocuronium bromide and morphine. All patients are given a total dose of tranexamic acid (TXA) at 30 mg/kg. Where patients have a pre-surgical creatinine >200 mmol/L, the dose of TXA is halved to 15 mg/kg. Prior to cardiopulmonary bypass, systemic anticoagulation is achieved with heparin given at a dose that achieves an activated clotting time (ACT) of greater than 400 seconds. Fresh frozen plasma (FFP) is administered if the target ACT is not reached. During cardiopulmonary bypass, haemoglobin (Hb) is kept at 60 g/L or above. Haemofiltration followed by RBC transfusion may be required to achieve this. Following cardiopulmonary bypass (CPB), protamine will be administered to reverse heparin, according to the dose of heparin given. Blood products may be used intra-operatively in the presence of excessive blood loss. RBC salvage will be used in all patients.

All patients have the new aortic valve assessed at the end of surgery using a transoesophageal echocardiogram (TOE). Details of this, as well as any additional surgical intervention, including conversion to conventional sternotomy from manubrium-limited sternotomy, and any further TOE are recorded.

#### Post-operative warfarin and aspirin administration

Post-operatively, all patients having a biological prosthesis begin 75 mg aspirin on the morning of the day following surgery. All patients having a mechanical prosthesis commence on warfarin on the evening of the day following surgery.

#### Post-operative assessments and procedures

The post-operative period (and trial protocol in relation to RBC and other blood product transfusions) begins once the patient has been admitted to the Cardiac Intensive Care Unit (CICU). Residual blood after cardiopulmonary bypass that has been bagged may all be given as a transfusion intravenously; the transfusion of this residual blood is commenced prior to CICU admission.

### Blood and blood product usage following surgery

The post-operative RBC transfusion and blood product transfusion processes for this trial begin from the point of admission to the CICU. All residual blood from the CPB reservoir and cell salvaged blood is returned to the patient; the following transfusion processes are implemented following complete transfusion of this blood and continue until a patient is discharged following their index operation.

Trial patients receive a RBC transfusion if at least one of the following criteria is met:Their Hb is <80 g/L.A diagnosis of post-operative bleeding is made as defined by ≥400 ml/h blood loss or ≥100 ml/h for ≥ 4 h with Hb ≥80 g/L.Blood loss leading to haemodynamic instability occurs irrespective of thromboelastography (TEG) and clotting profile results.

Trial patients receive a blood product transfusion if both of the following criteria are met:A diagnosis of post-operative bleeding occurs as defined by ≥400 ml/h blood loss or ≥100 ml/h for ≥ 4 h.TEG or coagulation guided transfusion is indicated.

Clinicians are able to transfuse, or decide not to transfuse, in violation of the protocol parameters; their reason for doing so will be recorded.

### Outcomes

#### Primary outcome

The primary outcome is the proportion of patients who receive a RBC transfusion post-operatively and within 7 days of AVR surgery.

#### Secondary outcomes

Secondary outcomes are:The proportion of patients who receive a RBC transfusion during the intra-operative period and the entire post-operative hospital stayThe mean number of RBC units transfused during the intra-operative period, post-operative period (within the 7 days following AVR surgery) and the entire post-operative hospital stayThe proportion of patients receiving blood product transfusions during the intra-operative period, within the 7 days following AVR surgery and during the entire hospital stayThe mean number of blood product transfusions received during the intra-operative period, within the 7 days following AVR surgery and during the entire hospital stayMean post-operative blood loss (millilitres) measured from chest drains at 6 and 12 hours, and at the time of drain removal, following AVR surgeryOperative success as defined by transthoracic echocardiographic assessment of left ventricular function, and degree of aortic regurgitation, within 6 weeks of AVR surgeryMean post-operative changes in haemoglobin (Hb) within the index hospital stayMean post-operative changes in inflammatory markers on admission to CICU and on day 1 following AVR surgeryProportion of patients reporting moderate or severe post-operative sternal wound pain, measured daily using an 11-point numerical rating scale developed by the trial team, until patient is fit for hospital discharge, and at 6 and 12 weeks following AVR surgeryRates of re-operation following index AVR surgery until 12 weeksRate of conversion to conventional AVR during index surgeryChanges in forced expiratory volume and forced vital capacity on days 3 and 4 and at 6 weeks following AVR surgeryEuroQoL EQ-5D-3L [21] scores, captured at baseline and on day 2, and 6 weeks and 12 weeks following AVR surgery, will be converted to health status scores using the value set (time trade-off) [22] and provide patient-level quality-adjusted life year (QALY) estimates as a health outcome [23]. The EQ-5D-3L is a validated, self-reported outcome measure consisting of five dimensions: mobility, self-care, usual activity, pain/discomfort, anxiety/depression. Each dimension has three levels of response.Mean time at which patients are fit for discharge from hospital following AVR surgeryHealth care utilisation during hospital stay and following discharge to 12 weeks, from medical note review, GP records and patient reportsCost and cost effectiveness estimated from QALY estimates and health care utilisation valued using national reference costs to 12 weeksRates of related adverse events during the 12 weeks following surgery including severity.

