### Blinding

This is a single-blind trial. Patients are not informed of the type of sternotomy they are planned to receive, or do receive, until completion of the pain assessment on day 2 following their operation. To enable blinding post-operatively, all patients have a trial-specific opaque dressing applied to their sternal wound and to their groin.

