#### Measures taken to avoid bias

This trial incorporates a number of methods to avoid bias:Concealment of allocation will be achieved through a web-based randomisation system, described above, managed by DCTU. Named clinical research team members enter a minimum data set per patient before individual allocation to type of sternotomy is provided.Three consultant cardiothoracic surgeons perform all operations as part of this trial. Each is expert in both techniques and does not delegate to other trainee or consultant surgeons.Criteria for blood and blood product transfusions are detailed in the protocol and followed for all patients. Clinical staff members in all cardiothoracic wards follow this protocol. Where clinical need requires blood to be given outside of the protocol, this is documented and described. The trigger for all transfusions is recorded.Patients are blind to the sternotomy procedure, both planned and received, for 2 days following their index surgery. All have an opaque dressing applied to both the sternum and the groin to facilitate blinding; these are only removed, and the patient informed, following their day 2 trial assessments unless clinical need requires earlier removal. Sternal wound pain is assessed using an 11-point numerical rating scale, with all analgesic medication taken in the preceding 4 hours recorded.Fitness for discharge is measured using defined physiotherapy and clinical criteria; these are assessed daily from day 3 by a research team physiotherapist and by the surgical research team. The date that both physiotherapy and clinical criteria are met is defined as the date the patient is fit for discharge. The date of actual discharge is also recorded.Where patients choose to withdraw from the study prior to 7 days following their index surgery, permission is sought to continue data collection to support analysis of the primary endpoint.

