#### Assessment of pain

Pain is assessed within 14 days prior to index surgery using an 11-point numerical rating scale. Pain is also assessed post-operatively (daily from post-operative day 2 until the patient is deemed ‘fit for discharge’), and at follow-up (6 and 12 weeks following discharge).

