### Statistical methods

The null hypothesis is that there will be no difference in the proportion of patients receiving RBC transfusion after manubrium-limited ministernotomy when compared to conventional sternotomy for AVR.

This trial will determine if manubrium-limited ministernotomy is an appropriate clinical alternative to the existing operation (conventional sternotomy) in terms of RBC transfusion requirements in the 7 days following index surgery. An analysis of the primary endpoint will be conducted using Fisher’s exact test. A sensitivity analysis will also be performed for the primary endpoint using a logistic regression model to account for potential confounders and stratification factors. Continuous outcomes will be analysed using general linear models. Correlation between repeated measures per patient will be appropriately accounted for in the linear models where applicable. Binary data will be analysed using logistic regression where there are no repeated data per patient. Repeated binary data will be analysed using generalised estimating equations. Stratification factors and chance baseline imbalances following randomisation will be explored for the primary and secondary outcomes.

Analysis will follow intention-to-treat principles with patients analysed according to the surgery allocated by randomisation and irrespective of surgery received, subsequent management or events [26]. Every effort will be made to retain and include all patients who receive surgery as part of the trial.

A prospective economic evaluation is integrated into the trial design and applies an NHS perspective to the inclusion of costs. Mechanisms of missingness within the data will be explored, and multiple imputation methods will be applied to impute missing data and minimise bias. Imputation sets will be used in bivariate analysis of costs and QALYS to generate incremental cost per QALY estimates and credible intervals [27–29]. It is anticipated that incremental costs and benefits will be captured within the trial, although extrapolated economic modelling will be considered if appropriate. Findings will be presented on the incremental cost-effectiveness ratio (ICER) plane and using cost-effectiveness acceptability curves (CEACs).

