## Discussion

This is the first trial to examine aortic valve replacement via manubrium-limited ministernotomy versus conventional sternotomy when comparing red blood cell transfusion rates following surgery. MAVRIC will determine if manubrium-limited ministernotomy should be adopted as best practice for patients requiring AVR surgery.

It was not possible to blind clinicians to the surgical procedure provided, although transfusion decisions are protocol-driven and should not be procedure-related. The inclusion of patient blinding was in response to a funding panel recommendation. It has been possible to implement this through the use of opaque dressing, which means that patient-reported pain scores at 2 days will be blinded. We will assess the effectiveness of blinding by inviting patients to indicate which treatment they think they have received before removing the dressings.

Surgical trials present significant challenges. The strengths of this trial include a rigorous research design, standardised surgery performed by experienced consultant cardiothoracic surgeons, an agreed anaesthetic regimen, patient blinding and consultant-led patient recruitment. Each discipline within the Cardiothoracic Division at JCUH is supporting and collaborating with the Chief Investigator. MAVRIC will demonstrate that complex surgical trials can be delivered to exemplary standards and provide the community with the knowledge required to inform future care for patients requiring aortic valve replacement surgery.

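### The one blinded pain reading (day 2) has no comparison of its own, and pain is defined only as a dichotomised proportion over readings that then become unblinded and stop at fitness for discharge

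*Protocol article*

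**What the plan says.** **Outcome.** Under Secondary outcomes, pain is a proportion (moderate or severe), "measured daily using an 11-point numerical rating scale developed by the trial team, until patient is fit for hospital discharge", with further readings at 6 and 12 weeks. Assessment of pain adds a pre-operative score on the same 11-point scale and sets the in-hospital readings as "daily from post-operative day 2 until the patient is deemed ‘fit for discharge".

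**Analysis.** Statistical methods states: "Repeated binary data will be analysed using generalised estimating equations". It names no time term, working correlation or contrast for pain. Continuous outcomes go to general linear models that allow for within-patient correlation.

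**Blinding.** Under Blinding, patients are not told their procedure "until completion of the pain assessment on day 2 following their operation". The Discussion claims only that "patient-reported pain scores at 2 days will be blinded".

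**Discharge.** Measures taken to avoid bias defines fitness for discharge by physiotherapy and clinical criteria, and "these are assessed daily from day 3 by a research team physiotherapist and by the surgical research team". Time to fitness is itself a secondary outcome. The section on the intervention says: "Potential benefits may include reductions in bleeding, post-operative pain, inflammatory response, hospital stay and time away from work".

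**The concern.** Three features of the stated pain outcome work against it.

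- **Blinding.** Pain is subjective self-report, and the opaque dressings protect it only up to day 2. The outcome covers day 2 and all later readings under one definition, so the protected comparison has no stated place of its own.
- **Stopping.** The daily series ends at a post-randomisation event that the intervention may bring forward. From day 3 the patients still being measured may differ between arms for reasons other than the effect of surgery on pain.
- **Information.** A 0-10 score and a baseline score are collected, but only a yes/no version is defined as the outcome.

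At stake is how far the trial's pain result can be trusted. Pain reduction is one of the benefits the protocol hopes for. The primary outcome is not affected.

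**Working it through.** **1. No pain figure to reproduce.** The only sizing figure is 260 patients for the primary outcome (30% against 13%, Fisher's exact test, two-sided 5%, 90% power). Exact enumeration at 130 per arm gives 90.2% power, so that figure is sound. The documents give no pain SD, cut-off, prevalence or length of stay, so every input in steps 3 and 4 is an assumption.

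**2. Readings set side by side.**

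| Reading | Patient blinded? | Cut off by fitness for discharge? |
|---|---|---|
| Day 2 | Yes, unless the dressing had to come off early | No; fitness is first assessed on day 3 |
| Day 3 until fit | No | Yes |
| 6 and 12 weeks | No | No |

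Day 2 is the only reading that is both blinded and untouched by the stopping rule.

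**3. Information kept by the cut.** For a normal score with a proportion p above the cut, the asymptotic efficiency of the binary version relative to the full score is φ(z_p)² / [p(1 − p)].

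- p = 0.5: 0.3989² / 0.25 = 0.637, so 260 patients carry the information of 260 × 0.637 ≈ 166.
- p = 0.3: 0.576, equivalent to about 150.
- p = 0.2: 0.2800² / 0.16 = 0.490, equivalent to about 127.
- p = 0.1: 0.342, equivalent to about 89.

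The loss is therefore 36% to 51% for p between 0.5 and 0.2, and larger for rarer pain.

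**4. Could early stopping bias a GEE?** Simulation with no true difference in pain on any day: 130 per arm, days 2 to 8, 300 runs per setting. Mean pain starts at 5 and falls 0.5 per day, with random-intercept SD 1.5, residual SD 1.2 and the cut at 4. Fitness is possible from day 3. Where stopping was made earlier in the intervention arm, that arm averaged about 0.6 to 1.1 fewer observed days. Entries are the odds ratio (above 1 means more pain in the intervention arm) and the rejection rate at 5%.

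| Stopping | No day term | Day terms, independence | Day terms, exchangeable |
|---|---|---|---|
| Same in both arms | 0.99-1.01; 5-8% | 0.99-1.00; 6-7% | 1.01*; 4-5% |
| Earlier in intervention, unrelated to pain | 1.15-1.29; 10-27% | 0.98-1.00; 4-5% | not available*; 5-6% |
| Earlier in intervention, and pain-dependent in both arms | 1.17-1.28; 14-28% | 1.08-1.14; 5-10% | 1.03-1.05; 2-3% |
| Pain-dependent in intervention only (extreme) | 1.05-1.60; 8-72% | 1.26-1.36; 21-33% | 1.01*; 6-7% |

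*Some exchangeable fits did not converge, so the mean odds ratio is missing in some settings and that column is indicative only. With 300 runs, the standard error of a true 5% rate is √(0.05 × 0.95 / 300) ≈ 1.3 points.

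So bias needs stopping to differ by arm, in timing or in how it depends on pain. It also needs either a model without day or stopping that depends on pain. Where it arises, it runs against the arm that is fit sooner.

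**5. Two inconsistencies found on the way.**

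- Blinding ends concealment after the day 2 pain score. Measures taken to avoid bias ends it after the day 2 assessments generally. The day 2 EQ-5D falls between the two.
- Secondary outcomes counts the 6- and 12-week pain readings from surgery. Assessment of pain has them "at follow-up (6 and 12 weeks following discharge"), and Participant timeline also counts from discharge.

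**The case against.** The strongest reply is that the selection bias is read into the plan. A reader might infer that GEE pools all days into a single odds ratio and that this ratio is therefore biased. The protocol does not say so. It names the method and no more; time terms, correlation structure and contrasts commonly sit in an analysis plan, which is not shown. With day terms and exchangeable correlation, the simulated bias was close to zero where pain affected stopping in both arms. Pain is not named as a fitness criterion, and a shorter stay is offered only as a possible benefit. The 6- and 12-week readings do not depend on fitness for discharge. All of this stands, and it reduces selection to a conditional risk for in-hospital days from day 3.

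It can also be said that the limit on blinding is openly disclosed, that nothing prevents a separate day 2 contrast, and that a proportion with moderate or severe pain is clinically readable in an unpowered secondary outcome. These are fair. The disclosure, however, makes it odder that the reading the dressings were meant to protect is not named as the comparison. Readability is kept if the proportion stays as a supporting display. The normal-score assumption behind the information loss is a simplification for a bounded 11-point scale, so 36-51% is a guide, not a measurement.

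**Conclusion.** The point holds in a limited form. From the text alone, pain is defined only as a dichotomised proportion, only day 2 is blinded, day 2 precedes any fitness-driven stopping, and day 2 is not singled out. The information loss is about 36-51%, assuming a normal score and 20-50% above the cut.

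Possible bias from day 3 until fitness rests on two unverified conditions: that stopping differs by arm, and that day is unmodelled or stopping depends on pain. The simulated odds ratios show what could happen under assumed inputs. They are not estimates of bias in this trial, and the documents do not support the stronger statement that the planned comparison is biased. This is an inexpensive improvement to a secondary outcome.

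**What to change.** 1. Name the day 2 score on the full 0-10 scale as the main pain comparison, using a linear model adjusted for baseline pain and the stratification factors.
2. Report 6- and 12-week pain as separate visit-specific contrasts, labelled unblinded.
3. Show in-hospital days from day 3 descriptively, or by a likelihood-based mixed model of the score with day terms. Such a model tolerates stopping that depends on scores already observed.
4. Keep the moderate/severe proportion as a supporting display.
5. Reconcile Blinding with Measures taken to avoid bias on whether unblinding follows the pain score or all day 2 assessments, including EQ-5D. Reconcile Secondary outcomes with Assessment of pain on whether 6 and 12 weeks run from surgery or from discharge.

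The cost is wording in the protocol or analysis plan. All the data are already being collected. The downside is that the daily in-hospital series loses its formal test.
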